### Statistical analyses

All data will be double-checked prior to statistical analyses. Baseline demographic and clinical characteristics of the participants according to groups will be analyzed using descriptive statistics, and inferential statistics will be employed to compare the effects of the dietary interventions on the different outcome measures. Continuous variables following a normal distribution will be expressed as mean ± standard deviation and asymmetrically distributed continuous variables will be expressed as median and interquartile range. Categorical variables will be expressed as absolute and relative frequencies. Departure of genotype distributions from the Hardy-Weinberg equilibrium in all participants will be assessed using chi-square tests. For between-group comparisons, analysis of variance (ANOVA) and the Kruskal-Wallis H test will be used for variables with normal and asymmetric distribution, respectively. The chi-square or Fisher’s exact tests will be used to evaluate categorical variables. All relevant endpoints (new cardiovascular events and death) will be registered as absolute number and percentages according to groups. The generalized estimating equations (GEE) model under the missing-at-random assumption will be used for comparison between outcome variables during the study period. Delta from all outcome data will be obtained from the difference between the measure at 12 weeks and baseline, and will be compared according to groups using analysis of covariance (ANCOVA), adjusted for potential confounders (for instance, differences in baseline data). The SNPs will be included in all ANCOVA models as interaction variables. There is no interim analysis planned. The significance level will be set at 5 %, and all data will be analyzed in SPSS 18.0 (SPSS Inc., Chicago, IL, USA) according to intention-to-treat.

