#### Laboratory variables

Blood samples will be collected by a trained professional at baseline and after 12 weeks. Samples will be centrifuged at 22 °C, 2000 rpm, for 10 min and stored in Eppendorf tubes at −80 °C for later analysis.

Lipid profile: total cholesterol, low-density lipoprotein cholesterol (LDL-c) and serum triglycerides will be evaluated by the enzymatic colorimetric method; high-density lipoprotein cholesterol (HDL-c) will be evaluated by the immunoprecipitation method (Roche Modular P Chemistry Analyzer®).

Inflammatory profile: interleukin-6 (IL-6), interleukin-10 (IL-10) and tumor necrosis factor alpha (TNF-α) will be evaluated by enzyme-linked immunosorbent assay (ELISA) using commercial kits (R&D Systems, Inc., Minneapolis, MN, USA), and according to the manufacturer’s instructions in a spectrophotometer (SpectraMax M2®). High-sensitivity C-reactive protein (hs-CRP) will be evaluated by the turbidimetric technique (Roche Cobas Integra 400 Plus Chemistry Analyzer®). Fibrinogen will be evaluated by the coagulometric method (Sysmex CA-600 systems®).

Glycemic profile: fasting glucose will be evaluated by the enzymatic colorimetric method (Roche Modular P Chemistry Analyzer®). Glycated hemoglobin will be evaluated by the immunoturbidimetric method (Roche Cobas Integra 400 Plus Chemistry Analyzer®). Serum insulin will be evaluated by electrochemiluminescence technique (Roche Elecsys 2010 Immunoassay Analyzer®).

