### Outcome measures

#### Primary outcome

The primary outcome measure will consist of changes in LDL-c (mg/dl) from baseline to 12 weeks.

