### Sample size

Sample size calculation was carried out in the WinPepi 11.20 for Windows program (Brixton Health, Israel). We used the data reported by Casas et al. [9], which assessed the effectiveness of a Mediterranean Diet pattern compared to a control diet among 164 individuals at high risk for cardiovascular disease. For a significance level of *α* = 0.05 and a statistical power of 80 %, with a between-group difference corresponding to a reduction of 13 mg/dl in the primary outcome (LDL-c) and considering no differences between olive oil and nut diets, the minimum sample size would be 171 patients (57 randomized to each group). Considering an expected loss rate of 20 % of patients, the total sample size needed will be 204 patients.

The allele frequency of the rs1761667 G>A and rs8069645 A>G SNPs in a Brazilian population is unknown. Since, in other studies, a frequency of approximately 40 % for each allele (A and G) has been found [23, 24], we expect that 204 individuals will provide a statistical power of 95 % in this analysis.

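### Baseline LDL-c is not a fixed covariate in the ANCOVA of change, and the only stated guide to adjustment is observed baseline differences

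*Protocol article*

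**What the plan says.** Under Primary outcome: "The primary outcome measure will consist of changes in LDL-c (mg/dl) from baseline to 12 weeks". Under Laboratory variables: "Blood samples will be collected by a trained professional at baseline and after 12 weeks". A baseline LDL-c is therefore planned for every patient.

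Under Statistical analyses, the change is built first: "Delta from all outcome data will be obtained from the difference between the measure at 12 weeks and baseline". These changes are then compared between groups by ANCOVA, "adjusted for potential confounders (for instance, differences in baseline data". That phrase is the whole covariate rule, except for the genetic terms: "The SNPs will be included in all ANCOVA models as interaction variables".

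The same section names a second longitudinal model: "The generalized estimating equations (GEE) model under the missing-at-random assumption will be used for comparison between outcome variables during the study period". It does not say how baseline enters that model.

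**The concern.** Randomisation makes any baseline difference between the three diet groups a matter of chance. Calling such differences confounders, and using them as the example of what to adjust for, points the analyst to a choice that can be made only once the baseline data are in hand. The covariate with an obvious claim to a place in the model, the baseline value of the outcome itself, has no guaranteed place in it.

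Two things are at stake. The first is precision on the primary outcome: an ANCOVA of change without the baseline value leaves in variance that the baseline value would remove. The second is prespecification: two analysts following the text faithfully could fit different primary models.

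This is more than detail left to an analysis plan. The article does state a criterion, and a plan that followed it would inherit the problem. The sentence on the SNPs shows that the authors fix model terms in advance when they mean to.

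**Working it through.** **Inputs from the article.** Difference 13 mg/dl, 57 per group and "statistical power of 80" % (Sample size); "The significance level will be set at 5" % (Statistical analyses).

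**Assumptions.** Two-sided test; one comparison of two arms of 57; equal SD s of LDL-c at baseline and 12 weeks; correlation r between the two, shown over 0.3 to 0.9. The article states neither r nor any SD.

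**Step 1: the plan's own figure.** The 57 per group cannot be reproduced without an SD; it can only be solved backwards:

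SD = 13 / [(1.960 + 0.842) × √(2/57)] = 13 / (2.802 × 0.1873) ≈ 24.8 mg/dl.

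The article does not say whether the SD it used was that of the raw change. The power figures below hold only if it was.

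**Step 2: variance with and without baseline.**

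- Raw change: 2s²(1 - r).
- Change adjusted for baseline: s²(1 - r²).
- Ratio, adjusted to raw: (1 + r)/2, so the reduction is (1 - r)/2.

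If the SDs are unequal (s₀ at baseline, s₁ at 12 weeks), raw minus adjusted variance is (s₀² + s₁² - 2r·s₀s₁) - s₁²(1 - r²) = (s₀ - r·s₁)². This is never negative, so the direction of the gain does not depend on the equal-SD assumption; only its size does.

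**Step 3: power at 57 per arm.** Power = Φ(2.802/√((1 + r)/2) - 1.960). At r = 0.7: 2.802/√0.85 = 3.039; 3.039 - 1.960 = 1.079; Φ(1.079) = 0.860.

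| r (assumed) | variance ratio | variance cut | power, if raw change has 80% | n per arm for 80% |
|---|---|---|---|---|
| 0.3 | 0.65 | 35% | 93.5% | 38 |
| 0.5 | 0.75 | 25% | 89.9% | 43 |
| 0.7 | 0.85 | 15% | 86.0% | 49 |
| 0.8 | 0.90 | 10% | 84.0% | 52 |
| 0.9 | 0.95 | 5% | 82.0% | 55 |

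**Step 4: an illustration of adjusting on imbalance.** The article gives no test or threshold for a baseline difference. As one possible trigger, a simulation (20,000 runs per setting, two arms of 57, SD of change 24.8) adjusted for baseline only when the baseline comparison gave p < 0.05, which happened in about 5% of runs.

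| r | power, adjust only if baseline p < 0.05 | power, always adjust | type I error, conditional rule |
|---|---|---|---|
| 0.5 | 80.2% | 88.9% | 4.2% |
| 0.65 | 80.5% | 86.1% | 4.7% |
| 0.8 | 79.6% | 83.0% | 4.6% |

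Under that assumed trigger nearly all the gain is lost, and the type I error is not raised.

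**Step 5: does the GEE supply the adjustment?** Not on the text. With LDL-c at baseline and 12 weeks and baseline treated as an unconstrained response, the group-by-time contrast is again the raw-change contrast.

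**The case against.** The case on the other side has several parts.

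- **The wording is open.** The article says for instance, which excludes nothing, including routine adjustment for the baseline value. A reader might infer that baseline LDL-c enters only when the arms differ, or only after a significance test. The text says neither. This stands: the defect is that baseline LDL-c is not fixed, not that it is barred, and Step 4 is an illustration only.
- **It is a condensed article.** A full covariate list commonly sits in the analysis plan. This stands for the list, but not for the stated link between adjustment and baseline differences.
- **The statisticians are blinded.** Randomization and blinding says that the staff doing the statistical analysis will not know the allocation. This limits steering the covariate choice towards a favoured diet. It does not prespecify the model or recover precision.
- **Validity is not at stake.** A reader might infer that the raw-change comparison is biased or that the error rate is inflated. Over randomisations the raw-change contrast is unbiased. Only given a realised imbalance does it shift, by (1 - r) times that imbalance: 0.5, 0.3 or 0.2 mg/dl per 1 mg/dl at r = 0.5, 0.7 or 0.8. The simulation showed no inflation with this single covariate.
- **ANOVA.** A reader might also infer that the changes are analysed by unadjusted ANOVA. The article names ANOVA for between-group comparisons in general and assigns the changes to ANCOVA.
- **The size is assumed.** This stands. No r or SD is documented, and at r = 0.9 the variance cut is only 5%.

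**Conclusion.** The point holds as one of precision and prespecification. The primary model does not fix baseline LDL-c, and its only stated criterion for adjustment is observed imbalance. Compared with always adjusting, a raw-change analysis carries variance that could be cut by 10% to 25% if r lies between 0.8 and 0.5 with equal SDs, or by 5% to 35% over r = 0.9 to 0.3. If the planned 80% power refers to the raw change, the gain at 57 per arm is to about 84% to 90% for r = 0.8 to 0.5. The documents do not support a claim of inflated type I error or of unconditional bias. This is an improvement available at no cost, not a flaw that invalidates the trial.

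**What to change.** Replace the covariate phrase under Statistical analyses with wording such as: *Each ANCOVA of a change will always include the baseline value of that outcome as a covariate (baseline LDL-c for the primary outcome), whether or not the groups differ at baseline. No covariate in the primary model will be chosen from observed baseline differences. Any other adjustment will be reported as a sensitivity analysis and labelled as such.*

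If the investigators want another fixed covariate, such as baseline use of lipid-lowering drugs, it can be named in the same sentence. That is optional.

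The cost is one or two sentences. Baseline values are already collected, and no visit, sample or patient is added. Trial status reports 120 patients already through the protocol with recruitment continuing, so the wording should be fixed and dated before outcomes are analysed by group.

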### Study objectives

The primary objective of this randomized-controlled clinical trial is to evaluate the effect of three dietary approaches on metabolic, inflammatory and anthropometric profiles in patients with CAD after 12 weeks. The secondary objective is to detect an interaction of patients’ response to these three dietary approaches with polymorphisms in the *CD36* and *STAT3* genes.

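### As written, diet-by-SNP interaction terms enter every ANCOVA, including the primary LDL-c model, so the diet term depends on SNP coding and loses precision to a degree that coding decides

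*Protocol article*

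**What the plan says.** All references are to the protocol article.

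- **Study objectives:** "The primary objective of this randomized-controlled clinical trial is to evaluate the effect of three dietary approaches" on metabolic, inflammatory and anthropometric profiles. Detecting an interaction between diet and the *CD36* and *STAT3* polymorphisms is the secondary objective.
- **Primary outcome:** "The primary outcome measure will consist of changes in LDL-c (mg/dl) from baseline to 12 weeks".
- **Sample size:** the calculation is made "with a between-group difference corresponding to a reduction of 13 mg/dl in the primary outcome (LDL-c"), and "the minimum sample size would be 171 patients (57 randomized to each group"). No interaction term enters it.
- **Statistical analyses:** the difference between 12 weeks and baseline is formed for all outcomes and compared between groups by ANCOVA. Then: "The SNPs will be included in all ANCOVA models as interaction variables". The same section also names ANOVA or Kruskal-Wallis for comparing groups and a GEE model for outcomes over the study period. It does not rank the three.

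The text names no ANCOVA without SNP interactions. It does not give the SNP coding, say whether the terms are centred, or say whether the two SNPs enter together.

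**The concern.** A rule that serves the secondary objective is applied to the model for the primary outcome. Once group-by-SNP terms are in a model, the group term no longer has one fixed meaning:

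- With SNPs as factors and the usual equal-weight test, it is an unweighted average over genotypes. At 40% allele frequency the 16% minor homozygotes then count as much as the 48% heterozygotes.
- With SNPs as uncentred 0/1/2 covariates, it is the diet effect in people who carry no copy of either coded allele.

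The primary objective asks for neither. If diet response does vary by genotype, as the investigators hope to show, the estimate itself moves. If it does not, the estimate is still less precise than the sample size section assumed. The stake is the power and the interpretation of the LDL-c comparison.

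**Working it through.** **Inputs.**
- From Sample size: a difference of 13 mg/dl, 57 per arm, and "a statistical power of 80" %.
- From Statistical analyses: "The significance level will be set at 5" %. I take this as two-sided.
- From Sample size: allele frequency of about 40% for each SNP, said to be unknown in Brazil.
- My assumptions: Hardy-Weinberg proportions (0.36, 0.48, 0.16), independent SNPs, a constant true effect of 13 mg/dl, and no gain from baseline adjustment.

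**The plan's own figure.** The article gives no SD. It takes its data from a cited study, "which assessed the effectiveness of a Mediterranean Diet pattern compared to a control diet among 164 individuals at high risk for cardiovascular disease". So 57 per arm cannot be reproduced independently. Solving n = 2(SD × 2.802/13)² for n = 57 gives SD = 13 × √(57/2)/2.802 = 24.77 mg/dl. The standardised effect is then 13/(24.77 × √(2/57)) = 2.802, and power is Φ(2.802 − 1.96) = 80%.

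**Effect of interaction terms.** If the variance of the diet-versus-control contrast is inflated by V, power is about Φ(2.802/√V − 1.96). The SD acts only through 2.802; V does not depend on it. Large-sample values of V:

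- Three-level factor, equal weighting, one SNP: (1/9)(1/0.16 + 1/0.48 + 1/0.36) = 1.235. Two SNPs: 1 + 2 × 0.235 = 1.47, power 64%.
- Dominant coding (64% carriers), equal weighting, one SNP: (1/4)(1/0.64 + 1/0.36) = 1.085. Two SNPs: 1.17, power 74%.
- Uncentred 0/1/2 (mean 0.8, variance 0.48), one SNP: 1 + 0.8²/0.48 = 2.33. Two SNPs: 3.67, power 31%.
- Centred 0/1/2: V = 1, power 80%.

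These are optimistic at this sample size. Only about 57 × 0.16 = 9 minor homozygotes are expected per arm, and their number varies by chance. Simulating genotypes gives the following at 57 per arm:

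| SNP terms | V, two SNPs | Power, two SNPs | Power, one SNP |
|---|---|---|---|
| None | 1 | 80% | 80% |
| Three-level, equal weighting | 1.74 | 57–58% | 68% |
| Dominant, equal weighting | 1.24 | 71% | 75% |
| Uncentred 0/1/2 | 3.81 | 30% | 44% |
| Centred 0/1/2 | 1.03 | 78–79% | 79% |

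Three-level coding centred on the observed genotypes gives 77% with two SNPs. Uncentred carrier coding gives 25%.

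**Sensitivity (two SNPs, equal weighting).** With 204 randomised and 20% lost, 204 × 0.8/3 is about 54 per arm: power is 78% without SNP terms, against 69% (dominant) and 56% (three-level). With all 68 per arm it is 86%, against 79% and 67%. Across allele frequencies of 0.3 to 0.6 at 57 per arm, equal-weight power ranges from about 36% to 78%.

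**Shift of the estimate.** Suppose the diet effect is d in non-carriers and changes by k mg/dl per allele of one SNP. The overall effect is d + 0.48k + 0.16 × 2k = d + 0.8k. Equal weighting gives d + (0 + k + 2k)/3 = d + k. Uncentred 0/1/2 coding gives d. The gaps are 0.2k and 0.8k per SNP, and both vanish when k = 0.

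**The case against.** - **ANOVA and GEE could supply a diet effect without SNP terms.** The SNP sentence is confined to ANCOVA, and the article does not call ANCOVA the sole or primary test. This stands in part: one cannot conclude that a real 13 mg/dl effect would be missed. But ANCOVA is the method tied explicitly to the 12-week-minus-baseline difference, which is how the primary outcome is defined, and no SNP-free version of it is named.
- **The sentence may be meant only for the secondary objective.** Interaction terms are appropriate there, and the article does not say that the diet effect will be read from that model. The text nevertheless says all ANCOVA models, so the reading rests on goodwill.
- **Coding and centring belong in an analysis plan that is not shown.** Agreed: their absence is not the point. The stated rule is.
- **A reader might infer that the plan cuts the power of the primary test from 80% to 58–71%.** The document does not support this. That range needs both SNPs entered jointly, equal weighting, a particular genotype coding, 40% allele frequency and a back-solved SD. Centred terms lose only one to three points, while uncentred 0/1/2 coding loses far more.
- **A reader might infer that the model necessarily answers a different question.** It does so only if an interaction exists. The power figures assume none, so they show lost precision alone.
- **A reader might infer a material loss of patients without a genotype call.** An ordinary ANCOVA would drop them, which sits uneasily with the stated intention-to-treat analysis. But no failure rate is given and blood is drawn at baseline, so the loss cannot be sized.

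**Conclusion.** The point holds as a defect of a stated rule. Taken at its word, the Statistical analyses section puts diet-by-SNP terms into the primary LDL-c ANCOVA, while the objectives make the interaction secondary and the sample size ignores it. The diet term then depends on coding: it is less precise in any case, and it differs from the overall diet effect if an interaction exists.

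The size is conditional. At 57 per arm with two SNPs, pairwise power lies between about 25% and 79%, according to coding choices that the article leaves open; one SNP per model gives about 68–75% under equal weighting. All figures rest on the assumptions listed in the working, chiefly the back-solved SD and the 40% allele frequency. None of them is a prediction of what the trial will do.

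**What to change.** State that the primary LDL-c ANCOVA, and the other ANCOVAs that estimate a diet effect, contain group and the baseline value of the outcome but no SNP interaction terms. State that diet-by-SNP interactions are tested in separate models for the secondary objective. Entering one SNP at a time there is a reasonable preference, not a requirement.

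If a single model is kept, centre the SNP terms, or average the diet effect over the observed genotype distribution, and say which.

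The cost is a change of wording and one extra model per outcome. No data collection or sample size change is needed.

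### Change in LDL-c goes to both a GEE model and an ANCOVA with neither named as deciding, and 34 SNP interactions are each tested at an unadjusted 5%

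*Protocol article*

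**What the plan says.** The protocol article names one primary outcome, change in LDL-c from baseline to 12 weeks (Primary outcome). The Sample size section assumes "with a between-group difference corresponding to a reduction of 13 mg/dl in the primary outcome (LDL-c") and "a statistical power of 80" per cent, "considering no differences between olive oil and nut diets", and arrives at "57 randomized to each group".

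The Statistical analyses section then gives three routes for comparing groups:

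- "For between-group comparisons, analysis of variance (ANOVA) and the Kruskal-Wallis H test will be used", the choice depending on the distribution.
- A GEE model, assuming data missing at random, for outcome variables over the study period.
- An ANCOVA on the 12-week change of all outcomes. Its covariates are given only by example (baseline differences), and the SNPs enter every such model as interaction terms.

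None is labelled primary. The only statement on error control is "The significance level will be set at 5" per cent. No pairwise diet contrast or post hoc procedure is written down. Detecting an interaction with the *CD36* and *STAT3* polymorphisms is the secondary objective (Study objectives), and the Sample size section attaches a power of 95% to the SNP analysis.

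**The concern.** Two stated analyses answer the same question on the same LDL-c data. If they disagree, the protocol gives no rule, so a claim could rest on whichever falls below 0.05. The ANCOVA has two further freedoms. Its covariates can be chosen after the data are seen. Because SNP interaction terms sit in the same model, what its diet effect means also depends on how genotype is coded.

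On the genetic side, two SNPs are tested against diet in the model for each outcome at a flat 5%. With that many tests, one or more significant interactions can be expected by chance. The protocol treats finding one as a formal objective with a stated power, so such a result could be reported as meeting it.

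This is more than detail left to an analysis plan: the article itself assigns the overlapping tests and the single 5% rule.

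**Working it through.** **The plan's own figure.** The protocol states no family-wise error rate to reproduce. Its sample size also cannot be recomputed, because no SD is given. For two groups of 57, a difference of 13, two-sided 5% (sidedness is not stated) and 80% power, the SD follows by back-solving:

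- Normal approximation: SD = 13 × √(57/2) / (1.960 + 0.842) ≈ 24.8 mg/dl.
- With the t distribution: SD ≈ 24.56 mg/dl, which is used for the power figures below.

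**1. Two analyses of one outcome.** Laboratory variables are taken at baseline and 12 weeks. With complete two-point data, the GEE group-by-time test is equivalent to a test on change scores. Simulation used 20,000 trials under no diet effect, 57 per arm, normal data and baseline as the only ANCOVA covariate:

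| Assumed baseline/12-week correlation | Change-score test | ANCOVA | Either significant |
|---|---|---|---|
| 0.3 | 5.0% | 4.9% | 7.7% |
| 0.5 | 5.1% | 5.2% | 7.6% |
| 0.7 | 5.0% | 5.0% | 6.9% |

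Each test alone holds 5%. Picking the better one gives about 7–8%. Free choice of further covariates is not included.

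**2. Three arms (conditional).** Under the null with equal arms:

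- One three-group test at 5%: 5.0%.
- Nut vs control and oil vs control, each at 5% with no gate: 9%.
- All three pairs at 5% with no gate: 12%.
- Pairwise tests only after a significant three-group test: 5.0%.

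**3. SNP interactions.** The outcomes listed under Primary outcome and Secondary outcomes are:

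- LDL-c 1 + other lipids 3 + inflammatory 4 + glycemic 3 + anthropometric 4 + blood pressure 2 = 17.
- 17 × 2 SNPs = 34 tests.
- Expected false positives = 34 × 0.05 = 1.7, whatever the correlation.
- P(at least one), independent tests = 1 − 0.95^34 = 0.825.

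With a common correlation among the 17 outcomes (an assumption; 40,000 draws per setting; interactions with 1, 2 or 4 df):

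| Assumed outcome correlation | P(at least one) |
|---|---|
| 0.3 | 74–76% |
| 0.5 | 62–65% |
| 0.7 | 46–50% |

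**4. Power under the remedy.** Both diets 13 mg/dl below control, SD 24.56, 57 per arm, 200,000 simulated trials:

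- 2-df three-group test: 83%.
- One diet-vs-control contrast, ungated at 5%: 80%.
- The same contrast, gated: 76%.
- The same contrast, Bonferroni for two contrasts: 71%.

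**The case against.** ANCOVA is the natural reading as the primary test: the outcome is a change from baseline, and the protocol defines exactly that quantity and gives it to ANCOVA. ANOVA and Kruskal-Wallis are alternatives by distribution, not two attempts, and that sentence may concern baseline comparisons. Both points are fair. They narrow the competition to GEE against ANCOVA but do not remove it, since the text labels neither and the ANCOVA itself is left open.

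Three stronger readings are tempting and are not supported:

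- **That the primary analysis runs at 9–12% error.** Those figures need ungated pairwise tests. The protocol writes none; its group tests are three-group comparisons, and one such test stays at 5.0%. The figures also come from the number of contrasts, not from competing models.
- **That a false interaction is nearly certain.** The 83% is the limit under independence, which cannot hold for outcomes such as weight and BMI, or total cholesterol and LDL-c. It is also the chance of at least one error in 34, while each test remains at 5%.
- **That the objective, worded as an effect "on metabolic, inflammatory and anthropometric profiles in patients with CAD after 12 weeks", creates several primary outcomes.** The Abstract, Primary outcome and Sample size sections all fix LDL-c as the only one, so that wording carries little weight.

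The Discussion does say the results may generate hypotheses for larger nutrigenetic trials. That softens the interaction point. But the Abstract and Discussion also say the authors will try to demonstrate modulation by genotype, and the formal objective and claimed power point the same way. The missing adjustment does not, however, touch the primary diet conclusion.

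**Conclusion.** The concern holds in a limited form and should be corrected. For the primary outcome, the defect is an undesignated choice between GEE and ANCOVA, worth about 7–8% error instead of 5%. That figure assumes complete two-point normal data, a baseline-only ANCOVA and baseline/12-week correlations of 0.3 to 0.7. The rates for ungated pairwise testing are a warning about a step the protocol leaves unspecified, not its stated error rate.

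For the secondary objective, 34 unadjusted tests yield about 1.7 expected false positives when no interaction exists. The chance of at least one runs from about 48% to 83%, depending on an outcome correlation that the protocol does not give.

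**What to change.** 1. Name one primary test: the 2-df diet effect on 12-week LDL-c, adjusted for baseline LDL-c, in a model without SNP terms, at 5%.
2. Test pairwise diet contrasts at 5% each only if that test is significant. With three arms this is a closed procedure and holds the overall error at 5%.
3. Call the GEE and any other LDL-c analysis supportive, and list any further covariates in advance.
4. For the SNP objective, formally test the diet-by-SNP interaction on LDL-c only, at 2.5% per SNP (5% / 2), in a separate model. Report the other 34 − 2 = 32 interactions as exploratory estimates with confidence intervals.

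This needs no extra patients, visits or assays. The price is a fall in power for a single diet-vs-control contrast from 80% to about 76%, at an SD of about 24.6 mg/dl that is back-solved and not stated in the protocol, and fewer interactions that can be called significant. Bonferroni over the two control contrasts would also control the error, but at about 71%. According to Trial status, 120 patients have completed and recruitment continues. No interim analysis is planned and the staff doing the statistical analysis are blinded to allocation, so the rule can still be fixed before unblinding.
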